## Abstract

**Background:**

Generalized anxiety disorder (GAD) is a prevalent anxiety disorder, with cognitive behavioral therapy (CBT) being the gold standard treatment. However, it is inaccessible and costly to many, as the mental health industry is overwhelmed by the demand for treatment. This means effective, accessible, and time-saving strategies must be developed to combat these problems. Web-based interventions for mental health disorders are an innovative and promising way to address these barriers. While electronically delivered CBT (e-CBT) has already proved productive and scalable for treating anxiety, other less resource-intensive interventions can be innovated. Checking up on mental health face-to-face has been shown to provide similar benefits to patients with anxiety disorders previously, but more research is needed to evaluate the efficacy of web-based delivery of this intervention.

**Objective:**

This study will compare the efficacy of e-CBT and a web-based mental health check-in program to treat GAD. These programs will both be delivered through a secure, web-based care delivery platform.

**Methods:**

We will randomly allocate participants (N=100) who are 18 years or older with a confirmed diagnosis of GAD to either an e-CBT program or a mental health check-in program over 12 weeks to address their anxiety symptoms. Participants in the e-CBT arm will complete predesigned modules and homework assignments while receiving personalized feedback and asynchronous interaction with a therapist through the platform. Participants in the mental health check-in arm will be contacted weekly through the web-based platform’s written chat feature (messaging system). Therapists will ask the participants a series of predesigned questions that revolve around a different theme each week to prompt conversation. Using clinically validated questionnaires, the efficacy of the e-CBT arm will be compared to the mental health check-in arm. These questionnaires will be completed at baseline, week 6, and week 12.

**Results:**

The study received ethics approval in April 2021, and participant recruitment began in May 2021. Participant recruitment has been conducted through targeted advertisements and physician referrals. Complete data collection and analysis are expected to conclude by August 2023. Linear and binomial regression (continuous and categorical outcomes, respectively) will be conducted.

**Conclusions:**

To the research team’s knowledge, this will be the first study to date comparing the efficacy of e-CBT with a web-based mental health check-in program to treat GAD. The findings from this study can help progress the development of more scalable, accessible, and efficacious mental health treatments.

**Trial Registration:**

ClinicalTrials.gov NCT04754438; https://classic.clinicaltrials.gov/ct2/show/NCT04754438

**International Registered Report Identifier (IRRID):**

DERR1-10.2196/48899

## Introduction

### Overview

Generalized anxiety disorder (GAD) is a prevalent and debilitating mental health disorder. More than 450 million people are living with mental and behavioral disorders, with many being unable to receive adequate treatment [1-3]. Cognitive behavioral therapy (CBT) is considered one of the first-line treatments for GAD; however, it is not without its drawbacks [4-7]. CBT is often inaccessible to patients because it requires in-person time commitment during work hours, travel to appointments, high costs, and potential exposure to social stigma [8]. CBT is extremely resource-intensive, requiring a large time commitment from a trained mental health professional. With the prevalence of mental health disorders as high as they are, the demand for this first-line therapy is not being met by North American health care systems, leaving them overwhelmed and patients unable to receive treatment [8,9]. Innovative interventions that optimize resources without sacrificing the quality of care are required to meet this demand.

Fortunately, web-based interventions for mental health disorders are growing in prevalence and are a promising way to address the barriers associated with in-person treatment, such as accessibility and convenience [10-15]. The structured nature of CBT has allowed it to be effectively adapted into a web-based format (electronically delivered CBT; e-CBT) where patients can access standard concepts remotely and in their own time. While e-CBT has already proven productive and scalable for treating anxiety disorders [10,16-19], developing less-intensive interventions that still benefit patients could allow for even more scalability. Not all patients may require the full structure of e-CBT and could still benefit from a less-intensive option, such as structured mental health conversations with a care provider. Checking in on individual mental health has previously shown benefits to patients with anxiety disorders, but much of this research has investigated in-person approaches and synchronous web-based deliveries [20-22]. Transferring this to a web-based asynchronous messaging format could allow for increased privacy, accessibility, temporal flexibility, and decreased cost and geographical barriers. Understanding how the delivery of e-CBT compares to a web-based delivery of mental health check-in conversations with a care provider can provide insight into the application of this as a viable intervention in the future.

### Objectives

The primary objective will be to compare the efficacy of an e-CBT program to a web-based mental health check-in program. Additionally, the individual effects of each treatment will be evaluated using clinically validated symptomology questionnaires.

## Methods

### Study Design

This study will use an open-label randomized controlled trial design to investigate the effects of e-CBT versus a web-based check-in program for GAD. Participants will be randomly assigned, in a ratio of 1:1, to either a 12-week e-CBT program tailored to GAD or a 12-week mental health check-in program to address their symptoms. In addition to these interventions, participants will continue with treatment as usual (ie, lifestyle, family physician appointments, and medications).

### Participants

Participants (total=100; e-CBT=50; and check-in=50) will be recruited in Kingston, Ontario, from outpatient psychiatry clinics at both Kingston Health Sciences Centre sites (Hotel Dieu Hospital and Kingston General Hospital). Additional recruitment from Providence Care Hospital, family doctors, physicians, clinicians, and self-referrals will occur. Once informed consent is obtained, participants will be evaluated by a psychiatrist on the research team through secure video appointments to make or confirm a diagnosis of GAD using the Diagnostic and Statistical Manual of Mental Disorders, 5th edition (DSM-5) [23].

Inclusion criteria include being aged 18 years or older at the start of the study, having a diagnosis of GAD according to the DSM-5 criteria by an attending psychiatrist on the research team, having the competence to consent to participate, having the ability to speak and read English, and having consistent and reliable access to the internet. Exclusion criteria include active psychosis, acute mania, severe alcohol or substance use disorders, and active suicidal or homicidal ideation. To avoid any confounding effect on the efficacy of this e-CBT program, participants currently receiving or having received CBT in the past year will also be excluded from this study to avoid confounding effects of treatment. If eligible for the study, participants will be randomly assigned to either the e-CBT program (n=50) or the mental health check-in program (n=50). Following the completion of the study, participants who were randomly assigned to the mental health check-in arm will be offered the e-CBT program if they are interested. During the informed consent process, it will be explained to all participants that this program is not a crisis resource and that they will not always have access to their therapist. In the case of an emergency, participants will be directed to the proper resources (ie, emergency department and crisis lines), and this event will be reported to the principal investigator.

### Procedures

#### CBT Arm

The e-CBT modules are designed to instill balanced and constructive coping strategies in participants. During the e-CBT program, the focus will be on essential thinking and behavioral skills to assist participants in becoming more engaged in day-to-day activities (Table 1). Additional focus will be placed on the connection between thoughts, behaviors, emotions, physical reactions, and the environment. All care providers are research assistants hired by the principal investigator. They all undergo training in psychotherapy delivery and additional training by the principal investigator on the research team, who is also a licensed therapist and an expert in web-based delivery, before interacting with participants. During this training, therapists complete feedback on practice homework, which is reviewed to ensure adequate quality of work. All care providers are supervised by a licensed therapist [10-12,16,24-26] who will review feedback before submission.

**Table 1 table1:** Overview of the 12-week electronically delivered CBT^a^ program content.

Week	Session	Description
1	What is generalized anxiety disorder?	Provides expectations for the course and introduces anxiety and CBT.
2	The 5-part model	Introduces the concept of the 5-part model and how a situation, thoughts, feelings, physical reactions, and behaviors are connected and how they interact.
3	Strategies for stressful situations	Provides an overview of helpful strategies that can be used in stressful situations, including pleasurable activities and helpful breathing techniques.
4	Situation, thoughts, feelings, physical reactions, and behaviors	Provides a further detailed exploration of the 5-part model and how changes in one area can affect the other 4 parts.
5	The thought record	Highlights the first 3 columns of the thought record; a tool used to help understand the connection between feelings, behaviors, and thoughts. The first 3 columns include the situation, followed by the feelings and automatic thoughts associated with it.
6	Automatic thoughts	This delves into the role of automatic thoughts and how they influence feelings. The focus of this session is to understand how to identify automatic thoughts and specifically identify the most dominant idea, or “hot thought,” when presented with a stressful situation. Common thinking errors are also discussed in this session.
7	Activity scheduling	Provides a break from learning about the thought record and instead explains how to use an activity record; a tool designed to record and plan weekly activities. This session focuses on how tracking activities can inform mood changes and reinforce the scheduling of pleasurable activities.
8	Evidence	Focuses on the fourth and fifth columns of the thought record, which are designed to help gather the information that supports or does not support the identified hot thought.
9	Alternative and balanced thinking	Focuses on the final 2 columns of the thought record, which reflect on the evidence columns to help find an alternative or balanced view of the situation. The last column invites the viewer to rerate their feelings based on the completion of the thought record.
10	Experiments	Explain the importance of conducting experiments to start believing alternative or balanced thoughts from the thought record and initiating changes in ineffective thinking patterns.
11	Action plans	Centered around identifying a problem that needs to be solved and provides a framework for creating a plan for solving the problem.
12	Review	The final session is a review of the course and summarizes the main CBT concepts and tools that have been taught throughout the program.

^a^CBT: cognitive behavioral therapy.

The e-CBT care plan consists of 12 weekly sessions of approximately 30 slides and interactive content, delivered through the Online Psychotherapy Tool (OPTT), a secure, web-based, cloud-based mental health care delivery platform. The e-CBT module content will mirror in-person standard CBT content, including different weekly topics, general information, skill overviews, and homework. Participants will be instructed to go through the content and complete homework at the end of the session, which will help them practice the skills they learned during that session. Homework will be submitted directly through OPTT and reviewed by the care provider assigned to the participant, who will provide personalized feedback within 3 days of submission. Care providers will have access to predesigned session-specific feedback templates to use as a basic structure to write their feedback. Doing so reduces the time needed to respond to each patient; therefore, the number of patients each care provider can handle increases. On average, developing this feedback will take a care provider 15-20 minutes per patient. In addition to the weekly feedback, participants have the option to message their care provider through the platform throughout the week regarding any questions or concerns they may have.

#### Mental Health Check-In Arm

Participants in the mental health check-in arm will have weekly interactions with a care provider through the chat feature in OPTT. The care provider will reach out weekly using structured question prompts to initiate interaction with the patient (Table 2).

**Table 2 table2:** Mental health check-in weekly procedures and question prompts.

Week	Topic	Question prompts
1	Mood	Tell me about yourself. How have you been feeling lately? How has the pandemic affected your mood? What differences have you noticed in your mood compared to the past?
2	Sleep	How have you been? Tell me about your week. I want to ask about your sleep. How many hours do you get? Do you feel rested? Do you think you need to make any changes to your sleep hygiene?
3	Activity	How was your week? How has your anxiety level been? What do you usually do to stay active during the day? Are there any indoor activities you can do at your place? Have you been using any online exercise programs?
4	Hobbies	What did you do in the past week? Do you have any hobbies? How long have you been doing them? Have you found any new activities that you enjoy recently?
5	Friendship	How was your week? How has the pandemic affected your relationship with your friends? Have you stayed in touch with your close friends during the pandemic? How often do you interact with your friends?
6	New events	How have you been? Have there been any new events in the past weeks? Are you planning to do anything new this week? Are you planning to do anything new this week? Are you expecting to hear any news from your family/friends?
7	Job and study	How have you been? Tell me about your week. How are you managing your day-to-day responsibilities (eg, job, school, personal, etc)?
8	Diet and food	How was your week? Let’s talk about your eating habits. How does your anxiety affect your appetite? Are you satisfied with your diet? How often do you cook? Do you prefer homemade food or take-out?
9	Books, movies, and television	How was your week? Has your anxiety affected your concentration? Do you like reading books? What is the last book you read? Are there any books you would recommend to your friends? What shows do you enjoy watching? What are some shows you would recommend to your friends?
10	Phone, apps, and games	Tell me about your week. How many hours a day do you usually spend on your phone? What is your favourite app? Do you play any games? What kinds of games do you like to play (eg, board games, cards, video games, etc)?
11	Habits	How have you been? How was your week? What do you think are some of your healthy habits? What are some habits you would like to change?
12	Accomplishments	How was your week? How did you find this program? Were the weekly check-ins helpful? Overall, was this program helpful for you? Why or why not? Are you interested in an online cognitive behavioural therapy program? Why or why not?

### Outcome Evaluation and Analysis

Participants in both arms will complete the following clinically validated questionnaires at baseline: State-Trait Anxiety Inventory (STAI) [27], Quality of Life Enjoyment and Satisfaction Questionnaire-Short Form (Q-LES-Q-SF) [28], Generalized Anxiety Disorder-7 item (GAD-7) [29], Depression Anxiety Stress Scale-42 item (DASS-42) [30], and a demographic questionnaire. All questionnaires will be completed through OPTT. The STAI, Q-LES-Q-SF, GAD-7, and DASS-42 will be completed again during week 6 and week 12. Using data from previous research incorporating this e-CBT program, a sample of 50 participants in each group was determined to be sufficient for an effect size of 0.5, a power of 0.8, and an α of .05 [31].

Before analysis, the data will be examined for missing, nonsensical, and outlying variables. Missing data will be removed on a per-protocol basis, with a statistical analysis significance level set at .05. Demographic information (ie, age, gender, and race) will be assessed between groups and program noncompleters using independent sample *t* tests. A 2×3 repeated measures ANOVA will be completed for each questionnaire score at the time points to investigate the differences between the 2 groups. An intention-to-treat analysis will be completed to assess whether the outcome of treatment impacts participants’ likelihood of not completing the program. Data will also be assessed with linear mixed-effects models with random effects as patient identification and fixed effects as treatment, time, and their interaction. SPSS (version 24; IBM Corp) will be used for all statistical analyses.

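### The 80% power claimed for 50 per arm at effect size 0.5 is not supported for a plain two-sided comparison (about 70%), and otherwise rests on unstated assumptions

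*Protocol article*

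**What the plan says.** All places are in the Protocol article.

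- **Outcome Evaluation and Analysis** gives the justification in one sentence: "a sample of 50 participants in each group was determined to be sufficient for an effect size of 0.5, a power of 0.8", with alpha .05. It attributes the figure to earlier research with the same e-CBT program.
- **Study Design** and **Participants** fix 1:1 allocation and the recruitment target: "Participants (total=100; e-CBT=50; and check-in=50) will be recruited". The target equals the number the power sentence calls sufficient.
- **Objectives** states the aim without a direction: "The primary objective will be to compare the efficacy of an e-CBT program to a web-based mental health check-in program".
- **Outcome Evaluation and Analysis** plans a two-group by three-visit repeated-measures ANOVA for each questionnaire, and in addition a linear mixed-effects model with treatment, time and their interaction. The significance level is .05. On incomplete data it says: "Missing data will be removed on a per-protocol basis".

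The article does not say whether the test is one- or two-sided, what kind of effect size 0.5 is, which outcome, visit and test the calculation used, what correlation was assumed, or what loss was expected.

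**The concern.** An effect size of 0.5, 80% power and a 5% level make a familiar combination. For two equal arms and a two-sided test it gives 63 or 64 per arm, not 50. The article puts all four numbers in one sentence, and under the most natural reading they do not agree.

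What is at stake is how a null result would be read. The Discussion envisages using the check-in program as a less resource-intensive option if it proves viable and effective. If the trial finds no significant difference and is described as 80% powered, readers may take that as fair evidence that the two programs perform alike. With power nearer 70%, or lower after loss, a missed difference of 0.5 SD is more likely than the stated figure suggests.

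**Working it through.** **Inputs.** n = 50 per arm, 1:1, alpha .05, target power 0.80 and effect size 0.5 are from the article. Reading 0.5 as a standardised mean difference d, and reading the test as two-sided, are inferences. Correlations and loss rates are assumptions, shown as ranges.

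**1. Can the stated figure be reproduced?** Normal approximation: n per arm = 2(z_alpha + z_power)² / d².

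- One-sided .05: 2(1.645 + 0.842)² / 0.25 = 49.5, so 50 per arm. The exact t calculation gives 51, with 79.9% power at 50. This reproduces the stated figure.
- Two-sided .05: 2(1.960 + 0.842)² / 0.25 = 62.8, so 63 per arm. The exact t calculation gives 64 (63 gives 79.5%). This does not.

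**2. Two-sided power at 50 per arm.** The noncentrality is 0.5 × √(50/2) = 2.5. The normal approximation is Φ(2.5 − 1.96) = Φ(0.54) = 70.5%; the noncentral t gives 69.7%. The difference detectable with 80% power is about 0.57 SD.

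**3. Repeated-measures group main effect.** Averaging three visits with common correlation r divides the variance by 3/(1 + 2r). For a 0.5 SD gap at every visit, the effective d is 0.5 / √((1 + 2r)/3).

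| r | total N for 80%, two-sided |
|---|---|
| 0.5 | 86 |
| 0.6 | 96 |
| 0.65 to 0.67 | 100 |

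So 50 per arm also follows from a two-sided main-effect formula at r of about 0.65. But that formula needs a 0.5 SD gap averaged over all three visits, one of which is the randomised baseline, where the expected gap is zero. If the gap instead builds 0, 0.25, 0.5 SD, the averaged gap is 0.25 SD and the main-effect test has about 30% power at r = 0.6 and 28% at r = 0.7.

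**4. Planned group-by-time test.** Assume gaps of 0, 0.25 and 0.5 SD at baseline, week 6 and week 12, equal correlations and 50 completers per arm. The deviations from the mean gap are −0.25, 0 and 0.25, with sum of squares 0.125. The noncentrality is (50/2) × 0.125 / (1 − r) = 3.125 / (1 − r), on 2 and 196 df.

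| r | noncentrality | power |
|---|---|---|
| 0.3 | 4.46 | 45% |
| 0.5 | 6.25 | 60% |
| 0.6 | 7.81 | 70% |
| 0.7 | 10.42 | 83% |

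A generic interaction formula with f = 0.25 and r = 0.5 asks for only 28 in total, but that f is a different effect. With a linear build-up to D at week 12, f² = D²/24, so f = 0.25 means D = √(24 × 0.0625) = 1.22 SD.

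**5. Baseline-adjusted week-12 comparison (not planned, for reference).** The effective d is 0.5 / √(1 − r²). With 50 analysed per arm, power is 80.1% at r = 0.47 and 81.5% at r = 0.5.

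**6. Loss (assumed rates), two-sample t test at d = 0.5.**

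| loss | analysed per arm | two-sided | one-sided |
|---|---|---|---|
| 0% | 50 | 69.7% | 79.9% |
| 10% | 45 | 65.0% | 76.1% |
| 20% | 40 | 59.8% | 71.6% |

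**The case against.** The strongest reply has four parts.

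*The sentence does not say two-sided, and 50 is right for a one-sided test.* The arithmetic stands: this is not a plain slip. But no directional hypothesis is stated, the objective is a comparison, and ANOVA F tests have no direction. A one-sided calculation at .05 does not describe the tests planned in the same section.

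*A two-sided calculation can also give 100 in total.* True, at a correlation of about 0.65 to 0.67. A reader might infer that 50 per arm can come only from a one-sided test; the documents do not support that. What remains is that this route assumes a gap which randomisation rules out in expectation at baseline. At correlations below about 0.65 the same formula makes 100 more than sufficient, but on the same assumption.

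*The 70% belongs to a test the article does not plan for its outcomes.* Also true. Independent t tests are named only for demographics. A reader might infer that the trial simply fails to deliver 80%, but the planned interaction test could exceed 80% at a correlation of 0.7 or more. The point is that the article gives no basis for choosing that value over 0.5, where power is 60%.

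*Sidedness, correlation and attrition may be in the full protocol, and the mixed model can use incomplete participants.* Both are fair. The point is therefore not that those details are absent from a condensed article, but that the figures it does state do not agree under the natural reading. The loss rates above are illustrations, not forecasts, and they apply to complete-case analysis. The mixed model would lose less, but the article presents it as an additional analysis.

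**Conclusion.** The point holds in this form: the stated 80% power is relied on, and the design as described does not support it without assumptions the article does not state. For an unadjusted two-sided .05 comparison at d = 0.5, 50 per arm gives about 70% power; 80% needs 63 to 64 per arm or a difference of about 0.57 SD. The two calculations shown above to return 50 per arm are a one-sided two-sample test and a main effect that counts a gap at baseline. Neither fits the stated aim and a randomised baseline.

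For the planned group-by-time test, power runs from about 45% to 83% over correlations 0.3 to 0.7, given a linear build-up to 0.5 SD and no loss. Any loss from a complete-case analysis lowers these figures; with 10% removed, even the one-sided two-sample reading falls to 76%.

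The 70% figure is firm arithmetic, conditional on reading 0.5 as a standardised difference and the test as two-sided. The rest depends on correlations and loss rates that the article does not give.

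**What to change.** Do not enrol more participants. Make one of two changes to the power sentence in Outcome Evaluation and Analysis.

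- **Restate it:** *50 per arm gives about 70% power for a standardised difference of 0.5 (two-sided .05, unadjusted) and 80% power for 0.57; power is lower with loss to follow-up.*
- **Or re-base it** on one named two-sided analysis, giving the outcome, the visit, the assumed correlation and the loss allowance. A baseline-adjusted week-12 comparison would support 80% for 0.5 SD with 50 analysed per arm if the baseline correlation is about 0.47 or more. That analysis would then also have to appear in the analysis plan. The correlation should be justified from the earlier data on this program, not chosen to reach 80%.

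The first change costs one sentence and no patients; its only downside is a less favourable stated figure. The second also needs the named analysis to be specified.

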## Results

The recruitment of participants for this study began in May 2021. Participant recruitment has been conducted through social media advertisements, physical advertisements, and physician referrals. To date, 50 participants have been recruited. Data collection is expected to conclude by August 2023, and data analyses are expected to be completed by September 2024, with linear regression analysis (for continuous outcomes) and binomial regression analysis (for categorical outcomes) being conducted.

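### Independent-sample t tests are assigned to gender and race as well as age; they suit age only, and for an unordered variable with more than two categories the p-value depends on arbitrary codes

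*Protocol article*

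**What the plan says.** Under Outcome Evaluation and Analysis, the protocol article lists the baseline instruments, "and a demographic questionnaire" among them. It then fixes the test: "Demographic information (ie, age, gender, and race) will be assessed between groups and program noncompleters using independent sample" t tests. The list is introduced by ie, not eg, so it reads as complete, and the same test covers all three variables and both comparisons (between arms, and for noncompleters). The threshold is given in the same paragraph: "with a statistical analysis significance level set at .05".

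The article does not say how many categories gender or race has. The only method for categorical data named anywhere is in Results (and in brief in the Abstract): "binomial regression analysis (for categorical outcomes) being conducted". That is reserved for outcomes and does not reach the demographic comparisons.

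**The concern.** A t test compares means, so it needs a variable whose mean has a meaning. Age has one. Race has unordered categories, and the mean of its numeric labels changes when the labels are reassigned. The same participants with the same answers could then be declared different or not different at .05 according to how the data file was coded.

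At stake is how far two descriptive comparisons can be read. The noncompleter comparison is the more important one. The same paragraph plans to remove missing data on a per-protocol basis, so a reader will want to know who was lost, and this is the only stated check of noncompleters' characteristics. It is a matter of a wrong method being stated, not of detail left to a fuller document.

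**Working it through.** **Inputs from the article.** t tests for age, gender and race, and a level of .05 (Outcome Evaluation and Analysis). 1:1 allocation (Study Design: "Participants will be randomly assigned, in a ratio of 1:1"). 50 per arm (Outcome Evaluation and Analysis: "a sample of 50 participants in each group was determined to be sufficient for an effect size of 0.5, a power of 0.8"). The planned comparisons have no figure of their own to reproduce. The sample size is the only computable figure in that section. It reproduces as 50 per group one-sided and as 63 two-sided (64 with the t distribution). That is a separate matter and nothing below depends on it.

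**Assumed, because the article gives none.** All category counts and proportions below, and the 80 v 20 split of completers and noncompleters.

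**1. Race with four unordered categories A, B, C, D.** Assumed counts: 30/10/5/5 in one arm and 30/2/5/13 in the other.

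*Chi-square.* Expected counts in each arm are 30, 6, 5 and 9. The statistic is 2 × (10 − 6)²/6 + 2 × (5 − 9)²/9 = 5.333 + 3.556 = 8.889 on 3 df, so p = 0.031. Relabelling the categories changes nothing.

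*t test.* t = (mean₁ − mean₂) / √[s² × (1/50 + 1/50)], where s² is the average of the two arm variances.

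| Coding (A, B, C, D) | Mean, arm 1 | Mean, arm 2 | s² | t | p |
|---|---|---|---|---|---|
| 2, 4, 3, 1 | 120/50 = 2.40 | 96/50 = 1.92 | (0.857 + 0.524)/2 = 0.691 | 0.48/0.166 = 2.89 | 0.005 |
| 1, 3, 2, 4 | 90/50 = 1.80 | 98/50 = 1.96 | (1.184 + 1.713)/2 = 1.448 | −0.16/0.241 = −0.66 | 0.51 |

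These are the two extremes of the 24 codings; 6 of the 24 (25%) fall below .05. The second coding even reverses which arm has the higher mean.

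Two other assumed tables behave alike:
- 20/10/10/10 v 20/20/0/10: chi-square p = 0.004; t test p from 0.001 to 0.44.
- 30/10/5/5 v 30/3/5/12: chi-square p = 0.084; t test p from 0.015 to 0.56.

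So the t test can miss a difference that chi-square finds at .05, and it can also report one that chi-square does not.

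**2. Gender with exactly two categories coded 0/1.** Here the mean is a proportion, and the pooled t statistic is a function of the uncorrected chi-square: t² = (N − 2)χ²/(N − χ²). Example with 35/50 v 25/50: χ² = 4.167, p = 0.0412; t² = 98 × 4.167/95.833 = 4.26, p = 0.0416.

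Exact enumeration for true proportions from 0.5 to 0.9 gave:
- Largest p-value difference between the two tests: 0.005.
- Type I error at 50 v 50: 0.048 to 0.057 for the t test, 0.050 to 0.057 for chi-square.
- Type I error at 80 v 20: 0.037 to 0.051 for both.

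**3. Gender with more than two categories.** The argument in step 1 applies unchanged.

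**The case against.** The best defence is that little follows from these tests. They describe demographics. They do not enter the repeated measures ANOVA, the mixed models or the sample size, and the article does not say that a significant result would trigger adjustment or alter the handling of missing data. A two-category gender item would do no harm, and race could be reduced to two groups or tested by indicator variables, in which case coding would not matter. All of this stands as a limit on the size of the point. It does not remove it: the article mentions no such reduction, and the test it names is wrong for race recorded in several categories.

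Some stronger readings are tempting but not supported:

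- *That the comparison is meaningless for gender as well as race.* The number of gender categories is not given, so two affected variables of three is an upper bound.
- *That recoding can move the p-value anywhere.* In the assumed tables the range is wide but bounded.
- *That this is the plan's main check on dropout.* The same paragraph also plans an analysis, labelled intention-to-treat, of whether treatment outcome affects the likelihood of not completing. That analysis does not look at demographics, but the article does not rank the two.
- *That baseline p-values must be dropped, or a model of non-completion with baseline severity added.* Testing randomised arms for baseline differences is uninformative, but dropping the tests is a reporting preference. Further modelling is an addition of the kind an article may leave to a fuller document.

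**Conclusion.** The point holds in a narrow form. The article assigns a test of means to a nominal variable and names no other test for demographics. For race the statement is wrong, assuming more than two unordered categories; for gender it is wrong only if more than two categories are recorded, and otherwise it is merely unconventional. The numerical size rests on assumed tables and illustrates the mechanism; it does not predict this trial's data. Severity is low: a reader might infer that the treatment comparison is compromised, but nothing in the article links these tests to it.

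**What to change.** Rewrite the sentence so that age is compared by the independent-sample t test, and gender and race by a chi-square test or, where expected counts are small, Fisher's exact test. Apply this both between arms and for noncompleters. The cost is one sentence. The baseline demographic data are the same, and no sample size or power figure changes.
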